**Methods:**

This study is a multicenter prospective block randomized controlled trial. A total of 74 patients with acute proximal isolated ACL tears will be assigned in a 1:1 allocation ratio to either (I) ACL repair using cortical button fixation and additional suture augmentation or (II) ACL reconstruction using an all-inside autologous hamstring graft technique. The primary objective is to assess if ACL repair is non-inferior to ACL reconstruction regarding the subjective International Knee Documentation Committee (IKDC) score at two-years postoperatively. The secondary objectives are to assess if ACL repair is non-inferior with regards to (I) other patient-reported outcomes measures (i.e. Knee Injury and Osteoarthritis Outcome Score, Lysholm score, Forgotten Joint Score, patient satisfaction and pain), (II) objective outcome measures (i.e. failure of repair or graft defined as rerupture or symptomatic instability, reoperation, contralateral injury, and stability using the objective IKDC score and Rollimeter/KT-2000), (III) return to sports assessed by Tegner activity score and the ACL-Return to Sports Index at two-year follow-up, and (IV) long-term osteoarthritis at 10-year follow-up.

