### Study design

This study is a multicenter prospective RCT with randomization into two treatment arms: (I) arthroscopic ACL repair with suture augmentation and (II) arthroscopic ACL reconstruction surgery. This study is a non-inferiority study with the hypothesis that arthroscopic ACL repair is non-inferior to (equivalent or better than) arthroscopic ACL reconstruction. All patients with proximal tears will be randomized during the operation into one of these treatment arms and will be followed up to 10-years postoperatively.

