### Sample size

The sample size calculation was based on the primary outcome of this study (subjective IKDC score), similar to another RCT design on this topic [65]. It has been shown that a difference of 8.8 points in the subjective IKDC score is the minimal clinically important difference (MCID) [76]. Using this non-inferiority limit of 8.8 points, and a standard deviation of 11 points [42, 65, 77] along with a two-sided alpha of 0.05, a power of 90%, and a lost-to-follow-up rate of 10%, a total of 37 patients in each group (74 patients in total) are needed to assess the primary outcome of this non-inferiority RCT. This sample size is also sufficient for the MCID of KOOS [78] and Lysholm score [79]. Given the recent studies that showed that 30-40% of the acute tears will have repairable proximal ACL tears [50, 80], we estimate that approximately 200 patients will be needed to be screened preoperatively to achieve the sample size of 74 patients [81].

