### Statistical analysis

Both an intention to treat analysis and per protocol analysis will be performed for this non-inferiority study. Comparison of nominal variables between ACL repair and ACL reconstruction will be performed using two-by-two tables with Pearson’s Chi-square test or Fisher’s exact test (in case one of the cells is < 5). For comparison of continuous variables, first tests for normal distribution of values are performed and independent t-tests are used of normal distributed values and non-parametric t-tests are used for not-normally distributed values.

A mixed model analysis for repeated measures will be performed to assess differences between both groups. Furthermore, a multivariate regression analysis will be performed for the primary endpoint of IKDC at two-years follow-up in order to correct for potential confounders. Statistical analysis will be performed using SPSS version 25.0 (IBM Software, Armonk, NY, USA). All tests are two-sided and a *p*-value of < 0.05 is considered statistically significant.

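### The analysis section sets a two-sided p < 0.05 rule for differences and does not tie the primary non-inferiority conclusion to the 8.8-point limit

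*Protocol article*

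**What the plan says.** The non-inferiority aim is stated several times. The Abstract (Methods) says: "The primary objective is to assess if ACL repair is non-inferior to ACL reconstruction regarding the subjective International Knee Documentation Committee (IKDC) score". The Study design section says: "This study is a non-inferiority study with the hypothesis that arthroscopic ACL repair is non-inferior to (equivalent or better than) arthroscopic ACL reconstruction".

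The limit itself appears in one place, the Sample size section: "Using this non-inferiority limit of 8.8 points, and a standard deviation of 11 points". The same sentence adds a two-sided alpha of 0.05, 90% power and 10% loss to follow-up, and arrives at 37 patients per group.

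The Statistical analysis section opens with "Both an intention to treat analysis and per protocol analysis will be performed for this non-inferiority study". It then names:
- chi-square or Fisher tests for nominal variables;
- t-tests or non-parametric tests for continuous variables, chosen after a normality check;
- a repeated-measures mixed model aimed at differences between the groups;
- a regression on two-year IKDC to adjust for confounders.

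It closes with one criterion for everything: "All tests are two-sided and a *p*-value of < 0.05 is considered statistically significant". The section contains no confidence interval for the treatment difference, no null hypothesis shifted by the margin, and no mention of 8.8 points.

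**The concern.** A non-inferiority trial succeeds by ruling out a deficit as large as the margin. A conventional test of no difference does not do that. A non-significant result may simply reflect imprecision. A significant result against repair could still lie wholly within 8.8 points.

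The section does more than leave the rule for later. It names the primary endpoint and the methods, and it fixes a significance rule for all tests. That rule does not match the stated objective. What is at stake is the primary conclusion. If the arms turn out similar, as the hypothesis expects, the written rule will nearly always return a non-significant result, and the article does not say how to get from there to a non-inferiority claim. The temptation would then be to treat non-significance as success. That reading becomes easier to satisfy as the data become noisier, and it does not hold the error rate at the margin to 2.5%.

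**Working it through.** **Inputs (Sample size section):** limit 8.8 points, SD 11, two-sided alpha 0.05 (one-sided 0.025 when read against a margin), power 90%, loss to follow-up 10%. The true difference is not stated; zero is assumed.

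**1. Reproduce the plan's sample size.**
n per arm = 2 × [SD × (z0.975 + z0.90) / margin]² = 2 × [11 × (1.960 + 1.282) / 8.8]² = 32.84, rounded up to 33.
With 10% loss: 33 / 0.9 = 36.7, rounded up to 37 per arm, 74 in total. This matches the plan exactly.
An ordinary two-sided test to detect an 8.8-point difference also gives 33, then 37. The number alone therefore does not show which test was intended. A one-sided alpha of 0.05 gives 27, then 30, and does not match.

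**2. Precision at the planned size.**
SE = 11 × √(2/33) = 2.708. With 64 degrees of freedom t0.975 = 1.998, so the 95% CI half-width is 1.998 × 2.708 = 5.41 points.

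**3. Where the two readings part (repair minus reconstruction).**
- Not significantly worse: observed difference above -5.41. At that point the lower CI limit is -5.41 - 5.41 = -10.82, beyond the limit.
- Lower CI limit above -8.8: observed difference above -8.8 + 5.41 = -3.39.

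An observed difference between -5.41 and -3.39 would be non-significant without excluding an 8.8-point deficit.

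**4. Operating characteristics (noncentral t, 33 per arm, SD 11).** Significance for repair requires T > 1.998. The margin rule uses the same cut-off after adding 8.8 to the difference; at a true difference of zero its noncentrality is 8.8 / 2.708 = 3.25.

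| True difference | Significant in favour of repair | Not significantly worse | Lower CI limit above -8.8 |
|---|---|---|---|
| 0 | 2.5% | 97.5% | 89.3% |
| -4.4 | under 0.1% | 64.0% | 36.0% |
| -8.8 | under 0.1% | 10.7% | 2.5% |

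The second column is the only result of the written test that would by itself imply non-inferiority. The third column shows what would follow if non-significance were taken as success.

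**The case against.** The strongest reply is that this is a condensed article. The full protocol or an analysis plan may say how the margin is to be read, and the named methods do not rule that out. A t-test, mixed model or regression each gives a mean difference and a confidence interval that can be set against 8.8, and a two-sided alpha of 0.05 fits a two-sided 95% interval used that way. The limit is also tied to the primary outcome in the Sample size section.

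Much of this stands. The sidedness is not the fault, and neither is the sample size. Which of the ITT and per-protocol results must succeed is something an analysis plan could settle, so its absence is not counted here.

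The reply does not cover the stated rule. The section speaks for all tests and directs the mixed model at differences. A margin-based rule held elsewhere would have to be reconciled with that wording.

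A reader might go further and infer that the plan adopts p > 0.05 as its success criterion, or that it can never establish non-inferiority. The document supports neither. Its closing sentence defines statistical significance, not non-inferiority. A significant advantage for repair would also imply non-inferiority, although under true equality that happens in only 2.5% of trials.

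**Conclusion.** The concern holds as a mismatch between the objective and the stated analysis: the trial sets out to show non-inferiority within 8.8 points, and the analysis section describes tests of difference without using that limit. When the arms are equal, the written test has a 2.5% chance of a result that validly implies non-inferiority, against 89.3% for the margin rule.

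The 10.7% false-pass rate at a true deficit of 8.8 points, against 2.5%, is conditional. It applies only if non-significance were read as non-inferiority, which the document does not say.

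These figures rest on the plan's SD of 11, 33 evaluable patients per arm, an unadjusted t comparison and, for the power figure, a true difference of zero.

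**What to change.** Add a primary decision rule to the Statistical analysis section:
- Non-inferiority is concluded if the lower limit of the two-sided 95% confidence interval for the mean difference (repair minus reconstruction) in two-year subjective IKDC lies above -8.8.
- The interval comes from one named primary model that estimates a mean difference. A rank test does not give an estimate that can be set against 8.8 points, so it should not serve as the primary analysis.
- The ITT and per-protocol results are expected to agree.
- The two-sided p < 0.05 rule applies to superiority and other comparisons, and a non-significant difference is not evidence of non-inferiority.

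The cost is wording, to be settled before outcome data are seen. The planned 37 per arm suits the rule on a single analysis set: power at zero difference is 89.3% by the t distribution and 90% by the normal approximation. If success is formally required in both sets, power may be slightly lower. The article gives no exclusion rate from which to calculate by how much.

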## Discussion

This study reports on the study design of the REPAIR-trial (**R**epair versus r**E**construction for **P**roximal **A**nterior cruciate l**I**gament tea**R**s). Few studies have examined the outcomes of repair versus reconstruction with favorable outcomes for ACL reconstruction [22–24]. However, these studies were performed over 30 years ago and are limited by the fact that all tear types were repaired rather than only proximal tears and that repair was performed using an arthrotomy [9, 25, 82]. Recently, four RCT studies have been designed to assess the outcomes of ACL repair [65, 83–85] but these are either performed in midsubstance tears [65, 83], assess the outcomes of dynamic intraligamentary stabilization (DIS) versus ACL reconstruction [65, 83], repair versus DIS [84] or Bridge-Enhanced ACL Repair (BEAR) with reconstruction [85]. Our current RCT differs from these studies as only proximal tears will be treated rather than all tear types and as the ligament will be reattached to the femoral footprint in a minimally invasive way.

The renewed interest of repair of proximal tears can be explained by improved understanding of patient selection. Research has shown that proximal tears have a better vascularity compared to midsubstance tears [26] and therefore have excellent healing capacity by reattachment to the femoral wall which is similar to the healing capacity of MCL tears [27]. Both historical studies on open ACL repair [9, 25, 82] and more recent studies on repair with DIS (also known as Ligamys) have shown that the clinical outcomes are indeed better when repairing proximal tears. Two studies have shown failure rates of repair with DIS in midsubstance tears of 24% in all patients and 36% in competitive athletes with midsubstance tears [86, 87]. Our current study applies strict patient selection criteria of proximal tears and good tissue quality. As the length of distal remnant and possibility of repair can only be assessed intraoperatively, randomization in this study should perform during surgery after the surgeon has confirmed the possibility of repair. Consequently, patients will be consented that they might be excluded during surgery if a non-repairable tear is present, and these patients will undergo standard ACL reconstruction.

It should be noted that there is also a potential disadvantage of ACL repair. By performing ACL surgery in the early phase (since early surgery prevents ligament retraction and preserves tissue quality that is both needed for repair [4, 5, 88]), it is likely that too many ACL surgeries will be performed. Current day standards recommend that patients following ACL injury will be treated conservatively first as approximately half of the patient may be copers and do not need surgical intervention [53, 60, 89]. By performing surgery on all ACL injured patients, patients will undergo surgery while they might be copers and do not need surgery. This risk is minimized in this study by only including patients aged 18 – 50 and only patients that desire to return to sports. It would be best if it is known preoperatively which patients will not do well with conservative treatment and ultimately require ACL surgery, as this both increases the chance of performing ACL repair and as early reconstruction outcomes decreases the risk for meniscal and chondral damage [60] at longer follow-up when compared to delayed reconstruction.

Several studies have recently reported good short-term outcomes of arthroscopic ACL repair using different techniques: in some studies femoral fixation consisted of using two suture anchors [42, 44], one suture anchor (for both bundles) [40, 45, 46] or transosseous tunnels with or without cortical button fixation [39, 41, 43, 55, 90], and some studies used ACL repair without [40, 41, 45, 46] or with [39, 43, 55, 90] additional suture augmentation. For this study, femoral fixation will consist of cortical button fixation with additional suture augmentation (FiberTape) in order to protect the repair in the early phases of rehabilitation, becuase it has been suggested that additional suture augmentation leads to lower rerupture rates [42, 48].

This study has been designed to assess the outcomes following repair and reconstruction of proximal ACL tears. We hypothesize that the repair treatment is a good treatment for proximal tears as it has potential advantages over ACL reconstruction: the surgery is short and minimally invasive, it has a low complication rate, rehabilitation is easier, and in case ACL repair fails then primary reconstruction surgery can be performed. Non-inferiority of arthroscopic ACL repair compared to arthroscopic ACL reconstruction may lead to a treatment algorithm in which patients with proximal avulsion tears can be repaired in the acute setting whereas patients with midsubstance tears will undergo ACL reconstruction in either the acute or delayed setting [91, 92].

## Data Availability

Available at study publication.

## Abbreviations

ACL: Anterior Cruciate Ligament
ACL-RSI: Anterior Cruciate Ligament - Return to Sports Index
BEAR: Bridge-Enhanced ACL Repair
DIS: Dynamic Intraligamentary Stabilization
FJS: Forgotten Joint Score
IKDC: International Knee Documentation Committee
KOOS: Knee Injury and Osteoarthritis Outcome Score
MCID: Minimal Clinically Important Difference
MCL: Medial Collateral Ligament
PROM: Patient-Reported Outcome Measure
RCT: Randomized Controlled Trial
REPAIR-trial: **R**epair versus r**E**construction for **P**roximal **A**nterior cruciate l**I**gament tea**R**s trial
SPIRIT: Standard Protocol Items: Recommendations for Interventional Trials
